### 2) Meeting with participant's occupational physician and supervisor

The occupational physicians will be asked to schedule a meeting with the participant, the participant's supervisor, and with himself/herself to make a return-to-work plan. Medical information from the hospital regarding disease, treatment, and long-term side effects as the identified barriers to return-to-work and actions to remove these barriers that were discussed with the nurse can be used as a basis for this discussion. This meeting should be scheduled between the second and third meeting with the nurse, which would be between the second and tenth month after the first day of sick leave. The researcher will request this meeting; the request will be attached to the first letter from the treating physician to the occupational physician. A return-to-work plan will contain the following information: first day of work resumption, the number of hours the participant will work, the task(s) he/she is going to perform, and with which steps patients will increase working hours, working days and/or will do additional or different tasks.

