### Randomisation, blinding and treatment allocation

The researcher will carry out randomisation using the computerised randomisation program ALEA [26]. Allocation of each patient is definite in such a way that allocation concealment is not possible. Because, patients differ significantly between the participating hospital departments in diagnosis and demographic factors, and because these aspects, as well as age, are important prognostic factors for return-to-work, [18] randomisation is stratified by the treating hospital department and age to prevent bias due to unequal randomisation. The cut-off age for stratification is 50. To equalise group sizes, minimisation is applied. If a treating hospital department has more than one nurse, participants in the intervention group will only be seen by nurses who carry out the intervention and vice versa. Participants, nurses, and researchers are not blinded to group assignment. Because all follow-up questionnaires will be filled out at home, no direct influence by the researchers is likely to occur.

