### Training nurses to carry out the intervention

The nurses who carry out the intervention will participate in a half-day training course. This training course consists of education about the rights and obligations of sick-listed employees according to the Improved Gatekeepers Act and education about the return-to-work problems of cancer patients. For instance, education about the return-to-work rates of cancer patients, factors that can have an impact on the return-to-work outcomes (e.g. diagnosis, type of treatment, and work ability), and the role of colleagues, supervisors, and occupational physicians. Furthermore, extensive practice is given at each meeting by means of role-playing and discussions between trainer and trainees. The training course will be given by a trained psychologist and a researcher. For evaluation, all nurses are asked to give their opinions of the training course by filling out an anonymous questionnaire at the end of the course.

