#### Effect evaluation

The study's effectiveness will be determined on the basis of the primary outcomes of return-to-work and quality of life and the secondary outcomes of work ability and work limitations, assessed at the long-term follow-up at 12 months and at the very long-term follow-up at 24 months. Prognostic factors will be taken into account in the effect analysis only if there are imbalances between the intervention group and the control group. Effectiveness will be inferred if participants in the intervention group will have a significantly shorter time to return-to-work than participants in the control group and if at the same time their quality of life does not significantly deteriorate. Return-to-work is measured both as the number of calendar days between the first day of sick leave and the first day at work (either part-time or full-time) sustained for at least 4 weeks and as the rate of return-to-work at follow-up. The first day of sick leave, the number of calendar days until return-to-work, and the return-to-work rates will be based on patient self-reporting on questionnaires [23]. Quality of life will be assessed with the SF-36 [31]. All subscales of the SF-36 will be taken into account (physical functioning, role limitations due to physical health problems, bodily pain, general health perceptions, vitality, social functioning, role limitations due to emotional problems, and general mental health). The SF-36 has been validated in a sample of cancer patients, and normative values have been determined [31]. Work ability will be assessed with the first 3 questions of the Work Ability Index (WAI) [32]. These questions concerns the evaluation of current work ability compared to their life time best and current physical and mental work ability with respect to their job demands. Acceptable measures for reliability and validity have been determined [33,34]. Work limitations will be assessed on the basis of the Work Limitation Questionnaire, where work limitations are defined as being inversely related to productivity [35]. This questionnaire consists of four different subscales: work scheduling, physical demands, mental demands/social demands, and output demands. The English version of the Work Limitation Questionnaire has been proven valid and reliable in populations of several chronic diseases [35] and cancer survivors [10,11,36]. The validity and reliability assessments of the Dutch translation of the Work Limitation Questionnaire are currently underway for healthy controls and cancer patients.

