### Statistical analysis

#### Effectiveness

All analyses, which will be performed to distinguish differences between the control group and intervention group, will be performed according to the intention-to-treat principle. All baseline data and data regarding primary and secondary outcomes will be presented using descriptive statistics. The number of days until participants' return-to-work will be analysed using the Kaplan-Meier survival method, and differences between groups will be tested with a log rank test. If necessary, the differences between the control group and the intervention group will be adjusted with a Cox regression analysis for confounders such as diagnosis and for the prognostic parameters. Longitudinal multilevel analysis will be used to examine differences between the control group and the intervention group with regard to improvement of the primary outcome of quality of life and the secondary outcomes of work ability and work limitations.

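### Home completion of questionnaires limits researcher influence only while the patient answers; deriving the return-to-work date and deciding on adjustment stay open to avoidable risk of bias

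*Protocol article*

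**What the plan says.** In the Protocol article, *Randomisation, blinding and treatment allocation* is open about the lack of masking: "Participants, nurses, and researchers are not blinded to group assignment". The only safeguard it then gives is "Because all follow-up questionnaires will be filled out at home, no direct influence by the researchers is likely to occur".

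The same section states "The researcher will carry out randomisation using the computerised randomisation program ALEA". Under *Meeting with participant's occupational physician and supervisor* we read "The researcher will request this meeting; the request will be attached to the first letter from the treating physician to the occupational physician", and under *Training nurses to carry out the intervention*, "The training course will be given by a trained psychologist and a researcher".

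Under *Effect evaluation*, effectiveness is inferred from a significantly shorter time to return to work, provided quality of life does not significantly deteriorate. The time runs from the first day of sick leave to "the first day at work (either part-time or full-time) sustained for at least 4 weeks", and is based on patient self-report. The same section allows prognostic factors into the analysis only where the arms are imbalanced. *Statistical analysis, Effectiveness* plans a log rank test and adds: "If necessary, the differences between the control group and the intervention group will be adjusted", by Cox regression, naming diagnosis as one example of a confounder along with the prognostic parameters.

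**The concern.** The safeguard addresses one route by which knowledge of the arm can reach the result, and the text goes no further. Once the form comes back, someone has to settle interrupted spells of work, trial working and incomplete dates against the four-week rule. Someone also has to judge whether an imbalance is large enough to adjust for, and which covariates enter. If these decisions are made with the arm visible, they can drift in one direction without anyone intending it. They bear on the time-to-return comparison that decides effectiveness. Treatment cannot be masked in this trial, but these two steps can be, so this part of the risk is avoidable.

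**Working it through.** **Step 1. What home completion covers.**

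| Step | Who the article says does it | Covered by home completion? |
|---|---|---|
| Answering the follow-up form | The participant, unblinded | Researcher influence: yes. Participant's own knowledge of the arm: no |
| Deriving first sick day, first working day and four-week confirmation | Not stated | No |
| Taking diagnosis and treatment from patient files | Not stated | No |
| Judging imbalance and choosing covariates | Not stated | No |

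**Step 2. What the researchers know.** They run the randomisation, request the meeting, co-train the intervention nurses and, under *Process evaluation*, rate nurse adherence. Allocation is therefore known within the team. No masked role is named in the article.

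**Step 3. How open the later steps are.** Forms arrive at 6, 12, 18 and 24 months, and a date with a four-week condition must be read from them. For adjustment, *Prognostic and descriptive factors* lists 14 prognostic factors and *Sample size* expects 5 to 10 in the final model. No threshold for imbalance is given and the covariate list is not closed.

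**Step 4. The plan's own figure.** Inputs from *Sample size*: 36% and 19% not returned at 18 months, 80% power, two-sided 0.05. With pooled variance and mean rate 0.275:

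n = [1.96 × √(2 × 0.275 × 0.725) + 0.842 × √(0.36 × 0.64 + 0.19 × 0.81)]² / 0.17² ≈ 107.1, so 108 per arm.

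This agrees with the stated total of 216 and is within one patient of the stated 109 per arm. The design figure is not in dispute; 108 per arm is used below.

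**Step 5. Illustration for the binary 18-month rate.** Assume no true effect and 36% not returned in both arms, so 0.36 × 108 ≈ 39 non-returners per arm. Let a share m of those in the intervention arm only be recorded as returned. Then q = 0.36 × (1 − m), the spurious difference is d = 0.36 − q, and with p̄ = (0.36 + q)/2:

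- SE₀ = √(2 p̄(1 − p̄)/108)
- SE₁ = √((0.36 × 0.64 + q(1 − q))/108)
- rejection rate = 1 − Φ((1.96 SE₀ − d)/SE₁) + Φ((−1.96 SE₀ − d)/SE₁)

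For m = 10%: q = 0.324, d = 0.036, SE₀ = 0.0646, SE₁ = 0.0645, giving 0.080 + 0.006 = 0.086.

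| m (assumed) | Patients (m × 39) | Spurious difference | Two-sided rejection |
|---|---|---|---|
| 5% | about 2 | 1.8 points | 5.9% |
| 10% | about 4 | 3.6 points | 8.6% |
| 20% | about 8 | 7.2 points | 20.4% |

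**Step 6. Illustration for the adjustment choice.** If the more favourable of the adjusted and unadjusted results were reported, and the two test statistics had correlation ρ (assumed), the two-sided error under bivariate normality would be 6.5% at ρ = 0.95, 7.0% at ρ = 0.90 and 7.8% at ρ = 0.80.

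The documents give no frequency of unclear records and no value of ρ. Step 5 concerns a binary rate, whereas the planned test is a log rank test on time. Many unclear records would move a date without changing returner status, so Step 5 does not measure the risk under the planned test.

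**The case against.** The defence has real force on several points.

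- The sentence is hedged. It says only that direct influence by researchers is unlikely, and it follows a plain statement that nobody is blinded. A reader might infer that the article claims home completion makes up for the lack of blinding altogether. It does not claim that.
- A reader might infer that the researchers themselves code the outcome and choose the covariates. The relevant sections are in the passive voice and assign these tasks to nobody.
- A reader might infer that the researchers deliver part of the intervention. They request a meeting and co-train nurses. The nurse, treating physician, occupational physician and supervisor carry out the components.
- A full protocol or analysis plan may name a masked analyst and rules for unclear records. Their absence from an article is no fault.
- Deleting the arm column does not mask someone who ran the randomisation, and no masking of derivation removes reporting bias from unblinded participants.

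All of this stands, and it limits the claim. It does not remove what the article itself fixes: a reassurance that stops at the completed form, and two adjustment triggers that leave the choice open.

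**Conclusion.** The point holds as a risk of bias that could be reduced at little cost. It does not show that bias is present: direction and size are unknown, and the figures in Steps 5 and 6 are illustrations under assumed inputs. They show only that a handful of records, or a free choice between two analyses, can move the error rate noticeably.

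The conclusion rests on three things in the article: all parties are unblinded, the only safeguard ends when the form is completed, and the four-week rule and adjustment triggers leave room for judgement. It does not depend on who performs those steps. If a fuller document already provides masked derivation and a closed covariate set, only the reassuring sentence and the two trigger statements need correcting. The trial remains interpretable either way, but the change has to come before arm-labelled outcome data are examined, because masking cannot be restored afterwards.

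**What to change.** 1. Limit the sentence on home completion to the filling-in of questionnaires, and state that self-report by unblinded participants remains a limitation.
2. Derive first sick day, first working day and four-week confirmation by a fixed script on a file with re-coded patient identifiers and no arm code. Re-coding is needed because removing the arm column alone does not mask a researcher who ran the randomisation. Keep intervention-only items, such as satisfaction and compliance, in a separate file.
3. Settle unclear records on that file and log the decisions.
4. Replace the imbalance trigger in *Effect evaluation* and the conditional wording in *Statistical analysis, Effectiveness* with a covariate set fixed before the arm code is added, for example the stratification factors (department and age) plus diagnosis. Say openly that this supersedes the imbalance rule, and state whether the log rank test or the adjusted Cox model decides.
5. Add the arm code only after the derived dates and the covariate set are locked.

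The cost is protocol wording, file handling, custody of the re-coding key by someone not deriving the outcome, and slightly later access to arm-labelled data. No extra patients or visits are needed.

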### Sample size

The calculation of sample size is based on two earlier studies regarding return-to-work in cancer patients. Based on the study by Spelten et al. [18] with consecutive cancer patients, the expectation is that 18 months after diagnosis 36% of patients will not have returned to work [18] after care as usual in the control group. With regard to the intervention group, the expectation is that 19% of the patients will not have returned to work 18 months after diagnosis [23], based on the study by Nieuwenhuijsen et al. [23]. Due to the inclusion and exclusion criteria, a percentage of patients with relatively less severe return-to-work problems will not be included in this study and this may lead to less favourable return-to-work rates. However, our intervention is more comprehensive than in the study by Nieuwenhuijsen et al. [23] and thus the expectation is that the percentages of patients that will not have returned to work will be the same as in the study by Nieuwenhuijsen et al. [23]. This indicates an Odds Ratio of 0.41 of the intervention versus usual care for higher percentages of patients that are not returned to work, which is the same as an Odds Ratio of 2.4 of the intervention versus care as usual for higher return-to-work rates. Since, the incidence of outcome is more than 10%, the Odds Ratio overestimates the magnitude of the association and therefore, we calculated the Relative Risk based on the Odds Ratio [27]. This indicates a Relative Risk of not returning to work of 0.53 of the intervention versus usual care. Based on the PS Power and Sample size Program, with a power of 80% and two-sided significance level of p < 0.05, the sample size should be 109 patients in every arm, for a total of 216 patients [28]. Assuming that 20% of the initial patients will be lost to follow-up during the course of the study, 270 patients must be recruited to gather 246 patients at 24 months. To account for at least 10% missing data at baseline, 300 patients are intended to be included. Furthermore, a sample size of 300 will have sufficient power to be able to control for the prognostic factors in a Cox regression analysis since we assume that 5 to 10 variables will be included in the final model [17,18] and a sample size of 10 per included factor in a Cox regression analysis is considered sufficient [29].

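### Two figures in the sample-size paragraph contradict their neighbours: 270 recruits with 20% loss leave 216 patients, not 246, and 109 per arm totals 218, not 216 (minor; enrolment of 300 can stand)

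*Protocol article*

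**What the plan says.** All the figures are in the Sample size section of the protocol article.

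- Control arm: "the expectation is that 18 months after diagnosis 36% of patients will not have returned to work".
- Intervention arm: "the expectation is that 19% of the patients will not have returned to work 18 months after diagnosis".
- Effect measure derived from an Odds Ratio of 0.41: "This indicates a Relative Risk of not returning to work of 0.53 of the intervention versus usual care".
- Error rates: "with a power of 80% and two-sided significance level of p < 0.05".
- Result from the sample-size program: "the sample size should be 109 patients in every arm, for a total of 216 patients".
- Attrition: "Assuming that 20% of the initial patients will be lost to follow-up during the course of the study", followed by "270 patients must be recruited to gather 246 patients at 24 months".
- Final target: "To account for at least 10% missing data at baseline, 300 patients are intended to be included".

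No other part of the article restates or corrects these numbers.

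**The concern.** The paragraph moves in steps from a per-arm number to a total, then to recruits and to the enrolment target. Two of its figures do not follow from the ones beside them. Equal arms of 109 cannot add up to 216, and 20% loss from 270 cannot leave 246.

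This is the article's only sample-size justification, so its figures are the natural yardstick for retention over the two-year follow-up. As printed, it offers two incompatible benchmarks at 24 months: 246 retained (about 9% loss) or 216 retained (20% loss). A trial that ended with 216 would be exactly on its stated attrition assumption, yet would appear 30 patients short of the printed figure.

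**Working it through.** **Inputs** (all from the Sample size section): p1 = 0.36 not returned to work under usual care; p2 = 0.19 under the intervention; Relative Risk 0.53; two-sided α = 0.05 (z = 1.960); power 80% (z = 0.842); 109 per arm; total 216; loss 20%; 270 recruits; 246 at 24 months; 10% missing baseline data; 300 to be included.

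**1. Number per arm.** The formula is the usual uncorrected one for two proportions:

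n = [1.960 √(2 p̄(1 − p̄)) + 0.842 √(p1(1 − p1) + p2(1 − p2))]² / (p1 − p2)², with p̄ = (p1 + p2)/2.

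- With 36% versus 19%: p̄ = 0.275 and the difference is 0.17. n = (1.960 × 0.6315 + 0.842 × 0.6199)² / 0.17² = 107.1, rounded up to **108**. Total 216.
- With the stated Relative Risk: p2 = 0.53 × 0.36 = 0.1908 and the difference is 0.1692. n = (1.960 × 0.6318 + 0.842 × 0.6203)² / 0.1692² = 108.2, rounded up to **109**. Total 218.

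So the printed 109 reproduces from the Relative Risk, and the printed total of 216 reproduces from the two percentages. The sentence may combine the two; the article does not say which input was used. Other variants fit neither figure: 119 per arm with a continuity correction, 105 with unpooled variance, 85 one-sided.

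**2. Per arm to total.** 2 × 109 = 218, not 216. The total of 216 is 2 × 108.

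**3. Attrition.**

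- 270 × (1 − 0.20) = **216**, not 246. The excess is 30, and 30/216 = 14%.
- 246/270 = 0.911, which is 8.9% loss.
- 246 remaining after 20% loss would need 246/0.80 = 307.5, so 308 recruits.
- Other routes miss 246 as well: 300 × 0.80 = 240, and 216 × 1.20 = 259.2.

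**4. The rest of the chain.** 216/0.80 = 270 and 270/0.90 = 300, both exact. The figures 216, 270 and 300 fit together; 246 and 109 do not fit with them.

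**5. The chain if 109 per arm is right.** 218/0.80 = 272.5, so 273; 273/0.90 = 303.3, so 304. The target of 300 is then 4 short.

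**6. Power of the same two-proportion calculation with the 216 patients that 300 enrolled would leave (108 per arm).**

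| Assumed rates | 108 per arm | 109 per arm |
|---|---|---|
| 36% vs 19% | 80.3% | 80.7% |
| 36% vs 19.08% (Relative Risk 0.53) | 79.9% | 80.3% |

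**The case against.** The arithmetic is not in dispute; the strongest case on the other side is that it hardly matters. The operative number is 300 enrolled, and that follows exactly from 216 with the stated 20% and 10% allowances. No analysis or decision rule in the article uses 246, which is most likely a slip for 216. The 109/216 gap is 2 patients, trivial beside a rounded 20% loss and an allowance worded as at least 10%. All of this stands, and it is why the point is minor.

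A reader might draw three stronger conclusions that the article does not support.

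- *That the trial is underpowered, or must enrol more.* On the plan's own rates, 300 enrolled leave 216 patients and about 80% power under either input.
- *That the plan promises about 85% power.* The two-proportion formula does give 85.2% at 123 per arm (246 in total), but the article claims 80% and attaches no power to 246. That formula also uses 18-month rates, whereas 246 is a 24-month count. The Effect evaluation and Statistical analysis sections base effectiveness on time to return-to-work with a log rank test, where patients lost later still contribute events or censored time. Neither 216 nor 246 completers gives the power of that test.
- *That 109 is the error and 108 is right.* The text does not settle this, because 109 is what the stated Relative Risk of 0.53 produces.

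**Conclusion.** Wrong as written, of minor severity. Under the stated 20% loss, the expected number at 24 months from 270 recruits is 216; the printed 246 is 30 patients (14%) too high. Separately, 109 per arm and a total of 216 cannot both hold; the gap is 2 patients.

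The attrition contradiction needs only multiplication and rests on no assumption beyond the plan's own. The explanation of 108 versus 109 assumes the uncorrected two-proportion formula with pooled variance under the null; the article names the program but not the method or inputs. The power figures (80.3% and 79.9%) apply only to that sizing calculation, with the stated rates and equal arms.

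**What to change.** 1. Replace 246 with 216 as the number expected at 24 months from 270 recruits.
2. Check the input and output of the sample-size program, then print one chain:
   - **36% versus 19%:** 108 per arm, 216 analysable, 270 after the loss allowance, 300 enrolled; 80.3% power on the two-proportion calculation.
   - **Relative Risk 0.53:** 109 per arm, 218 analysable, which strictly needs 273 and then 304. If enrolment stays at 300, say that 216 are expected, with about 79.9% power.
3. State which input the chain rests on, and that the power refers to the two-proportion calculation and not to the log rank test.

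The cost is a few corrected figures and a sentence. Enrolment of 300 need not change; applying the second chain strictly would add 4 patients. The printed retention expectation becomes less favourable, by 30 patients.
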